## Abstract

**Background:**

Even before the COVID-19 pandemic, caregivers of children with rare neurogenetic conditions (NGCs) experienced physical and mental health challenges. These challenges escalated during the COVID-19 pandemic due to crisis-level breakdowns in support services. Tele–mental health and parenting support services expanded rapidly in response to the COVID-19 pandemic and may be well suited to facilitate necessary support interventions for NGC caregivers. However, it remains unclear how to match these evidence-based interventions to individual NGC caregivers’ needs.

**Objective:**

Project WellCAST (Supporting Well-Being of Caregivers via Telehealth) is an early-phase clinical trial designed to prospectively test which evidence-based telehealth interventions best meet the needs of NGC caregivers.

**Methods:**

Interested and eligible NGC caregivers are enrolled in a 24-week program with 5 phases, including baseline (2 weeks), support program (12 weeks), and follow-up (2 weeks) periods; a 4-week gap separates the phases. Caregivers participate in 2 randomizations, namely support program assignment via a precision health algorithm versus quasi-random assignment and motivational coaching by another NGC caregiver and project staff member (“peer coaching”) versus standard check-ins by a staff member who is not an NGC caregiver (“staff coaching”). Virtual support programs include acceptance and commitment therapy, dialectical and behavioral therapy, culturally informed cognitive behavioral therapy, research units in behavioral intervention, naturalistic communication intervention, Durand sleep intervention, and self-guided resources. A subset of caregivers will participate as waitlist controls before engaging in support programs. We developed and optimized a personalized health decision tree algorithm that matches caregivers to telehealth support programs. We then proceeded to test the feasibility and efficacy of algorithm-assigned support programs across 4 waves of data collection, relative to quasi-random assignment and waitlist controls. During each wave, the personalized health algorithm relies on 2 weeks of baseline data collection using clinical tools and innovative smartphone-based ecological momentary assessments. Across waves, we also test the efficacy of a motivational peer-to-peer coaching protocol, deployed by trained NGC caregiver staff, in enhancing support program uptake and clinical outcomes.

**Results:**

Four waves of data collection are scheduled for August 2023 to September 2025. Preregistered analyses will contrast feasibility, efficacy, and acceptability across algorithms and coaching assignments. Multiple waves of data collection will allow us to continually optimize the algorithm and test incremental improvements across project phases. Secondary analyses will probe the feasibility and efficacy of individual evidence-based support programs and peer coaching.

**Conclusions:**

Project WellCAST will test whether a digital personalized health decision tree algorithm and peer coaching protocol can prospectively enhance telehealth support program outcomes among NGC caregivers. This project is relevant to the specific population of NGC caregivers and may also inform how brief digital assessments, precision health tools, and community-academic partnerships can enhance the public health response to mental health crises across other high-need populations.

**Trial Registration:**

ClinicalTrials.gov NCT05999448; https://clinicaltrials.gov/study/NCT05999448 and OSF Registries 10.17605/OSF.IO/8WNDP; https://osf.io/8wndp

**International Registered Report Identifier (IRRID):**

DERR1-10.2196/64360

## Introduction

### Overview

Although tele–mental health and parent coaching services are increasingly available, it remains unclear which types of support programs are best suited to various populations and how to best deliver these support programs. One population particularly well suited to telehealth support programs is caregivers of children with neurogenetic conditions (NGCs). Here, we defined NGCs as genetic conditions that affect cognitive, psychosocial, and physical development; examples include named conditions, such as Angelman syndrome, Prader-Willi syndrome, and Williams syndrome, as well as rare and ultrarare conditions with lower prevalence rates. These NGC caregivers are vulnerable to elevated stress and mental health challenges due to often extreme caregiving burden; for example, they may experience geographic isolation from specialty support clinics, exhibit elevated levels of parenting stress, and manage complex child behavioral and medical needs with limited structural resources [1-3]. Project WellCAST (Supporting Well-Being of Caregivers via Telehealth) is a National Institutes of Health–funded clinical trial that aims to prospectively develop and test the efficacy of a precision health decision tree algorithm for routing NGC caregivers to evidence-based telehealth supports, based on their unique clinical and lifestyle profiles. Project WellCAST also tests the efficacy of community-engaged peer-to-peer coaching protocol in enhancing the feasibility and efficacy of digital supports. Here, we provide the rationale and protocol for Project WellCAST, including anticipated outcomes and impact within and beyond NGC caregiving communities.

### Project Background

Although telehealth support programs have existed for some time, telehealth services expanded rapidly in response to the COVID-19 pandemic [4], providing new opportunities for increased access to mental health programs [5,6]. One population for whom telehealth services offer critical benefits are NGC caregivers. Although the elevated mental health needs of NGC caregivers predated the COVID-19 pandemic [7], the pandemic caused them to face crisis-level breakdowns in support and intervention services that have continued to impact families [8]. These COVID-19 pandemic–related impacts were, in part, driven by social isolation, financial strain, and reductions in face-to-face support programs, which compounded an already fragmented and challenging landscape of care [2,3]. The COVID-19 pandemic–related interruptions required caregivers to take on even more responsibility as they managed urgent educational, vocational, and functional needs of their children [3]. The negative impact on caregivers’ health and well-being continues to this day [8]. However, despite their elevated need, caregivers rarely receive support for their own mental health. Any psychological support they do receive is typically disconnected from their child’s care plan and delivered by practitioners with little-to-no expertise in the needs of NGC families [9,10]. Consequently, accessible and scalable digital interventions are needed to support the intersectional needs of NGC caregivers and prevent an accelerated breakdown in their mental health, particularly in the wake of the COVID-19 pandemic.

In part due to the rapid and dramatic uptake in telehealth methods during the COVID-19 pandemic, many questions remain regarding the circumstances and populations for which telehealth services are most effective [6], including but not limited to services for NGC caregivers. Although a variety of evidence-based telehealth support programs are available, it is not always clear which programs should be provided to which patients. This issue has long motivated the psychiatry and psychology literature, though many randomized controlled trials continue to examine broad treatment effectiveness [11,12] rather than investigating treatment personalization protocols [13]. Precision health literature guides our efforts to move toward support program personalization for NCG caregivers, with promising examples of prognostic models in other populations [14].

One challenge to the effective prospective assignment of patients to treatments is the issue of measurement. Often, mental health providers base selection on limited intake information and through subjective assessment guided by broad symptom checklists or patient-reported symptoms. As an expansion of this approach, precision mental health care aims to optimally match patients to existing evidence-based treatments through the use of demographic, clinical, and dispositional information [14]. Tools such as daily diaries and ecological momentary assessments (EMAs) hold promise for providing temporally dense information about participants’ experiences, beyond the contributions of clinical assessments alone. EMAs are brief questionnaires aimed at gathering real-time data on the participants’ experiences that reduce the challenges of retrospection [15]. Using EMA data can provide insights into fluctuating daily experiences and momentary affects, as well as information about practical day-to-day constraints within their lives that may affect support program uptake (eg, caregiving burden, health behaviors, and social support). However, to date, tools such as EMA have not been prospectively used to match patients to support programs based on their personal health profiles.

Another consideration for the effective assignment of support programs is the impact of sociocultural and practical issues on a patient’s willingness and ability to engage in tele–mental health treatment. For example, several studies have documented that telehealth does not universally improve accessibility and may, in some cases, enhance preexisting disparities by disrupting trust and rapport, distancing communities with poor technology literacy or access, and introducing concerns about data security and privacy [16]. These health care gaps are amplified among Black and other minority families who are less likely to receive mental health care due to discrimination, racism, and historic injustices against Black people in health care settings [17].

One potential solution to the disrupted rapport in telehealth-based programs is to implement community-centered and motivational support programs, such as participation enhancement interventions aimed at addressing barriers to support program participation and enhance motivation and adherence to treatments [18,19]. These support programs may be particularly beneficial for caregivers of children with NGCs due to isolation and disconnection from social support that may accompany their child’s complex needs [9,10]. Peer support is known to provide benefits to caregivers [20,21], though to be most useful, perceived need and received support must align [22]. There is also some evidence that peer support may have differential impacts on certain subgroups of parent caregivers (eg, individuals with higher baseline anxiety [23]), though more evidence is needed to determine which participants might benefit most from peer support. Thus, peer support interventions may positively impact willingness and engagement in tele–mental health programs for some caregivers while simultaneously being an extra unneeded hassle for others. Although these programs have demonstrated broad efficacy across several neurodevelopmental populations, they have not been explicitly tested in substantial NGC caregiving samples. Given that coaching programs require extra time and resource commitments from both families and professionals, and many participants effectively engage in intervention without peer support, it is important to determine which participants would benefit from this extra layer of support.

### This Study

Project WellCAST (NCT05999448) is an early-phase clinical trial designed to prospectively test which evidence-based telehealth interventions best meet the unique needs of NGC caregivers. We accomplish two specific aims: (1) develop and optimize a personalized health decision tree algorithm to match NGC caregivers to digital health programs using a combination of standard clinical tools and smartphone-based EMA data, and (2) test the efficacy of peer-to-peer coaching, deployed by trained NGC caregivers using an evidence-based motivational interviewing protocol, in enhancing support program uptake and clinical outcomes. Here, we describe the protocol methods and anticipated impact of this project, both for NGC caregivers and the broader field of precision mental health.

## Methods

### Study Design

Project WellCAST uses a randomized control design with waitlist control to test the effectiveness of both (1) a precision health algorithm and (2) a participation enhancement intervention on improving clinical outcomes for NGC caregivers. It is anticipated that between 500 and 750 caregivers will enroll in WellCAST across waves, with a minimum enrollment of 500 participants, including 50 waitlist controls, to adequately power primary analyses. SPIRIT (Standard Protocol Items: Recommendations for Interventional Trials) reporting guidelines were used in the preparation of the Project WellCAST protocol [24].

Project WellCAST is deployed across 4 waves. During waves 1 and 2, participants are randomly assigned to be routed to support programs using either a preregistered precision health algorithm (algorithm 1) or quasi-random assignment. During waves 3 and 4, participants are assigned to support programs using optimized algorithms (algorithms 2 and 3, respectively). Across waves 1 to 4, participants are randomized to either a participation enhancement intervention delivered by an NGC caregiver coach (peer coaching) or similarly timed check-ins by non-NGC caregiver staff (staff coaching).

At the time of the initial protocol submission, Project WellCAST has completed waves 1 and 2 (fall 2023 and spring 2024); waves 3 and 4 will be conducted in fall 2024 and summer 2025, respectively. Thus, across waves, 25% of participants are assigned to each algorithm category (quasi-random, algorithm 1, algorithm 2, and algorithm 3), and 50% of participants are assigned to each peer coaching category (peer coaching and staff coaching).

### Ethical Considerations

#### Overview

Project WellCAST was determined to present no more than a minimal risk of harm to participants. The study was approved by the Purdue University Institutional Review Board (IRB) on March 3, 2023 (2022-1058); collaborating sites deferred oversight to Purdue as the single IRB of record. Participants provide informed consent before engaging in baseline data collection and later provide informed consent specifically for their assigned support program before engaging in sessions.

#### Compensation

Caregivers are paid US $100 for completing assessments. There are 5 sets of forms total, and the amount of compensation increases over time to maximize response (baseline: US $10; start of programs and mid support programs: US $15 each; end of programs: US $30; and follow-up: US $30). Participants are not compensated for time spent in support programs. Participants who are participating in the waitlist control receive compensation as they would if they participated in a support program. Payment is delivered using Amazon gift cards after participants complete each set of forms, and support programs are delivered free of charge.

#### Privacy and Confidentiality

Participants provide a variety of personal health information data, including medical and genetic records and psychiatric diagnostic information. We are not subject to the Health Insurance Portability and Accountability Act (HIPAA) guidelines, as we are not a medical entity. However, we use HIPAA-compliant data storage tools and procedures whenever possible. Data are stored on password-protected and encrypted devices, HIPAA-compliant Microsoft Box folders, and the HIPAA-compliant data management system REDCap (Research Electronic Data Capture; Vanderbilt University) [25,26]. Participant data are labeled by identification numbers rather than name, wherever possible. Only key study personnel have access to REDCap, where identification numbers are stored alongside participant information. Otherwise, identification numbers are stored separately from personal information.

#### Plan for Documenting Potential Protocol Modifications

Potential deviations from protocol and protocol modifications are logged into a protocol deviation log by the research team. Applicable protocol modifications will be submitted to the IRB for review at each instance. The research team will complete a yearly audit of the registered protocol on all platforms.

### Trial Registration

Project WellCAST was registered on ClinicalTrials.gov on August 21, 2023, and the first algorithm was registered on Open Science Framework (OSF) Registries on August 30, 2023, before running the first algorithm assignment. The first participant consented to a support program on August 31, 2023, and the first participant started the support program on September 11, 2023. Supplemental analytic plans were preregistered on OSF Registries on October 18, 2023, to further detail the ClinicalTrials.gov registration. Wave 1 participants consented to baseline data collection starting June 28, 2023, and started baseline data collection on August 7, 2023. Baseline data were collected before any participant consented to support programs and were not analyzed or used to route participants until after registration was complete.

### Recruitment

Caregivers of children with NGCs are recruited through various sources to maximize the potential participant pool. Recruitment strategies include social media advertisements, sharing materials with genetic clinics and providers, mailers by patient advocacy groups, emails to condition-specific email distribution lists, and recruitment through registries. Inclusion criteria are (1) legal guardian of an individual aged 2 to 35 years with a documented NGC associated with intellectual or developmental disability that is not primarily characterized by neurodegeneration, (2) fluent in English, (3) interacts with the individual with an NGC most of the time, and (4) resides in the United States. Participants are excluded if they either (1) express severe psychiatric illness not indicated for the interventions offered (eg, suicidal, psychotic thoughts, mania, or significant substance use) or (2) are currently in active therapy or receiving support that would conflict with, or be redundant with, the interventions offered.

### Screening

Interested participants may scan a QR code on recruitment materials or receive a link via email to a digital prescreening survey via REDCap [25,26]. Once complete, research staff members who are trained in clinical assessments contact interested caregivers by phone to conduct a screening interview and to determine eligibility. The research staff member verifies demographic information and assesses the participant’s recent mental health history using the Mini-International Neuropsychiatric Interview [27]. If the participant is determined eligible to participate, the research staff member provides instructions on how to sign electronic consent forms for the baseline phase of the project in REDCap and begins the baseline phase of the study. Participants separately provide consent to their specific support program after being assigned a program arm during the routing phase.

### Decision Tree Algorithm Development

#### Overview

The decision tree algorithm was designed to function as a clinical decision tree. The rules and explanations for the algorithm are coded into an R program, and each output is reviewed by our biostatistics team to ensure that the algorithm is working correctly.

#### Initial Decision Tree Algorithm

The algorithm, decision nodes, and thresholds are all preregistered on OSF Registries before use to promote transparency, explainability, and interpretability. Support program assignments are based on clinical and lifestyle data provided by participants in the 2-week baseline period. For example, in algorithm 1, participants who report high levels of emotional dysregulation, depression, stress, or anxiety will be eligible for adult-focused mental health programs. Once eligible for adult-focused mental health programs, participants are assigned to either individually delivered acceptance and commitment therapy (ACT) or group-based dialectical and behavioral therapy (DBT) based on their initial data. Participants with higher emotional dysregulation scores are routed to DBT, whereas participants with below-threshold levels of emotional dysregulation are routed to ACT. This threshold was determined via multiple data sources. A primary aim of the study is to evaluate and optimize the efficacy of these algorithms, and we anticipate that support program assignment criteria will evolve following preplanned algorithm optimizations, as will be detailed in peer-reviewed manuscripts describing study results. The full descriptions of all decision nodes and thresholds for each iteration of the algorithm are available in algorithm preregistrations on OSF Registries. We also anticipate that further justification for the support program assignment will be discussed in the peer-reviewed manuscripts describing study results after the trial has concluded.

#### Minimizing Bias

Any algorithm or assessment tool will exhibit bias toward its normative sample. To minimize this, we prospectively implemented several protective measures that are also aligned with guiding principles for addressing algorithm bias [28]. We planned algorithm optimization via a CASCADE (community-engaged approach for scientific collaborations and decisions) panel at 2 preplanned intervals. The CASCADE panel process was intentionally designed to minimize biases. The key pillars of the CASCADE approach include centering community input, minimizing opportunities for cognitive biases in decision-making, and centering diverse experiences and perspectives, particularly of individual patients [29]. CASCADE panels include representation from individuals with lived experience in the trial’s target population (eg, rare disorder caregivers) present and engaged in the process. A specific example approach for addressing bias during CASCADE panels includes examining scores and data trends for minoritized populations within our sample to minimize the potential for exacerbated disparities. We anticipate that future applications of our final algorithm will require substantial interrogation for generalizability to any new participant group.

### Routing Procedures

Participants are matched to a combination of digital health support programs using a multistep process indicated by the data provided in the baseline phase. First, research staff not involved in participant support programs generate an eligibility panel for each participant that contains feasible and appropriate programs based on broad rule out criteria. For example, participants who do not identify with minority groups will not be eligible for programs focused on race-related trauma. Participants with children aged >8 years are not eligible for certain child-focused programs designed for young children. The preregistered algorithm is then used to generate a sequential list of participants’ recommended programs, based on their baseline data.

During waves 1 and 2, the first randomization is to algorithm 1 or quasi-random assignment. Participants randomized to algorithm 1 are assigned their algorithm-indicated support program. If practical issues prevent them from engaging with their top program (eg, lack of availability during group times), they are offered the next indicated support program. Participants randomized to quasi-random assignment are assigned to a support program using a random number sequence generated by a member of the biostatistics team who is not involved in participant management or intervention deployment. Similarly, if practical constraints prevent their first program from being feasible, they are moved to their next program indicated by the random number sequence. Whether the participant received their top assignment is recorded and integrated into statistical analyses. Finally, all participants are randomized to either peer coaching or staff coaching protocols using a random number generator. During waves 3 and 4, participants continue to be randomized to peer coaching or staff coaching. All participants receive algorithm 2 during wave 3 and algorithm 3 during wave 4. Care providers are masked to the status of peer coaching and algorithm assignment. Peer coaches are masked to the status of algorithm assignment. Data managers and statisticians evaluating study outcomes are provided deidentified data and are not involved in support program–related study operations. Research team members evaluating study outcomes are also masked to assignments.

A subset of participants is also assigned to a waitlist control to allow for the evaluation of treatment efficacy and quantify potential attenuation of responses with repeated assessment [30]. Participants assigned to waitlist controls contribute identical data to active participants and receive the same remuneration. They are routed to support programs or resources during the next wave.

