**The Clinical Global Impression Scale (CGI)**
It is used to measure clinical impressions of severity (CGI-S) [61] and impressions of overall improvement since the start of support programs (CGI-I). Clinicians respond to a single item for each subscale, ranging from 1 (not at all ill or very much improved) to 7 (among the most extremely ill patients or very much worse since the initiation of treatment). The scale had strong internal consistency when used in a sample of adults with and without psychiatric conditions (CGI-S: α=.99; CGI-I: α=.94) [62].

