#### Interim Data Analysis for Algorithm Optimization

At 2 prespecified intervals, we assess the feasibility, acceptability, and efficacy of the routing algorithm and, broadly, Project WellCAST, in promoting the well-being of caregivers of children with NGCs. Following the CASCADE method for an interdisciplinary “think tank” process, we will use multiple data sources to inform each iteration of the algorithm to optimize and enhance effective triaging for support program implementation [29]. Tables 2-4 detail the metrics of feasibility, acceptability, and efficacy that will be the focus of each think tank, including the desired and undesired outcomes associated with each. Across metrics, we are specifically interested in predicting which individuals will respond suboptimally to the project so that we can proactively minimize these challenges in future versions of the algorithm.

The think tank will be attended by multiple project interest-holders, including NGC caregivers, project staff, clinicians, biostatisticians, and trainees. Before the think tank, biostatisticians will complete preregistered analyses, which will be presented alongside participant feedback and project interest-holder surveys. During the think tank, we will generate a list of hypotheses for how the algorithm can be improved; this list will be narrowed through a systematic process of (1) ensuring each change is supported by more than 2 sources of information (quantitative data, qualitative data, NGC community input, and past literature), (2) evaluating technical feasibility, and (3) ensuring each change is aligned with NGC community priorities. The output of each think tank will be a manuscript submission that justifies specific changes to the algorithm, as well as a preregistration of the resulting optimized algorithm, which will be used to route the subsequent wave of participants to support programs.

**Table 2 table2:** Optimal and suboptimal outcome categories across feasibility metrics^a^.

Feasibility categories		Desired outcome	Undesired outcome	Outcome coding

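### The statement that clinicians and peer coaches are masked to algorithm assignment can hold only in waves 1 and 2; for algorithms 2 and 3, informant ratings are effectively open

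*Protocol article*

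**What the plan says.** Routing Procedures in the protocol article makes two masking statements about the people who treat and coach participants: "Care providers are masked to the status of peer coaching and algorithm assignment" and "Peer coaches are masked to the status of algorithm assignment". Neither is tied to particular waves.

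The same section sets out the allocation. "During waves 1 and 2, the first randomization is to algorithm 1 or quasi-random assignment". After that there is no allocation between algorithms: "All participants receive algorithm 2 during wave 3 and algorithm 3 during wave 4". Coaching continues to be randomized in all four waves. Study Design repeats which wave uses which algorithm and gives the shares: "25% of participants are assigned to each algorithm category (quasi-random, algorithm 1, algorithm 2, and algorithm 3".

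Interim Data Analysis for Algorithm Optimization describes how each revised algorithm arises: "The think tank will be attended by multiple project interest-holders, including NGC caregivers, project staff, clinicians, biostatisticians, and trainees". The result is preregistered and then routes the following wave.

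Textbox 3 lists the informant-reported primary outcomes. Among them is the CGI (severity and improvement), for which "Clinicians respond to a single item for each subscale", and a 1-to-5 rating of program fit given by clinicians and peer coaches. Table 1 lists as primary only the DASS-21, PSI-SF and PSOC, all self-reported. The Results part of the abstract says that preregistered analyses will contrast feasibility, efficacy and acceptability across algorithms.

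**The concern.** A masking claim tells the reader how far a subjective rating can be trusted. The CGI items and the fit rating are single judgments, made by people who deliver the program or coach the participant. Someone asked how well a program fits, who knows that a revised matching algorithm chose it, may rate it differently from someone who does not know how it was chosen.

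As written, the article says that this knowledge is withheld for all four categories. If it is withheld for only two, a comparison of algorithm 2 or 3 with algorithm 1 or quasi-random assignment sets ratings made under different conditions against each other. A reader relying on the masking statement would not know it.

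**Working it through.** This is a check of one statement against another, with simple arithmetic for its reach.

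**Step 1. Reproduce the stated shares.** Assume four equal waves and 1:1 randomization in waves 1 and 2.
- Quasi-random = (0.25 + 0.25) × 0.5 = 25%
- Algorithm 1 = (0.25 + 0.25) × 0.5 = 25%
- Algorithm 2 = all of wave 3 = 25%
- Algorithm 3 = all of wave 4 = 25%

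This matches Study Design.

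**Step 2. Ask, wave by wave, whether there is anything to conceal.**

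| Wave | Routing methods in use | Can algorithm status be masked? |
|---|---|---|
| 1 | Algorithm 1 and quasi-random | Yes |
| 2 | Algorithm 1 and quasi-random | Yes |
| 3 | Algorithm 2 only | No: the wave identifies it |
| 4 | Algorithm 3 only | No: the wave identifies it |

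Clinicians and coaches hold sessions on the wave's schedule, so they know which wave they are in. The link from wave to algorithm is in the published design.

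**Step 3. Reach.** Categories in which status follows from the wave: 2 of 4, or 25% + 25% = 50% of participants. Study Design expects 500 to 750 participants, "with a minimum enrollment of 500 participants, including 50 waitlist controls, to adequately power primary analyses".
- Of 500: 250. Without the 50 waitlist controls: 450 × 0.5 = 225.
- Of 750: 375. Without 50 waitlist controls: 700 × 0.5 = 350.
- If waves 1 and 2 together hold 40% to 60% of participants (an assumed range), the share is 60% to 40%.

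These are upper bounds for the ratings themselves. Participants given self-guided resources use a journal, and no treating clinician is described for them. Peer-coach ratings exist only for those assigned a peer coach. At the stated 50%, taken to apply within each wave, that is 0.5 × 0.5 = 25% of participants for algorithms 2 and 3 together.

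**Step 4. Which outcomes.** The clinician-rated CGI and the clinician and coach fit ratings, both in Textbox 3. Table 4 also lists the CGI as the coding for coach-reported efficacy.

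**Step 5. What is not touched.** Algorithm 1 versus quasi-random assignment is randomized within waves 1 and 2, where masking is possible. Coaching is randomized in every wave, and having one algorithm per wave does not reveal a participant's coaching arm to the care provider.

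**The case against.** The strongest reply is that nothing randomized is harmed. Waves 3 and 4 contain no concurrent algorithm allocation to conceal, so the masking sentence may have been meant only for waves 1 and 2. Cross-wave comparisons are already non-randomized and mixed with calendar time, which masked raters would not cure. The article's explicit use of these ratings is in the think-tank tables, and the detailed analyses sit in a registry that is not shown. All of this stands, and it limits what is at stake. It does not rescue the sentence, which has no wave limit and follows directly on the one assigning a single algorithm to each of waves 3 and 4.

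Three stronger readings are tempting and are not supported:
- **That the raters helped design the algorithm they rate under.** Clinicians and trainees attend the think tank as role groups. The article does not say that these are the people who treat and rate in waves 3 and 4. The point does not need this.
- **That the ratings are biased in favor of the revised algorithms by some amount.** The article gives no rating standard deviation and no evidence on the size or direction of an expectation effect. Any figure would be an assumption.
- **That the trial's primary outcomes as a whole are unmasked by this.** Textbox 3 calls the informant ratings primary, but Table 1 names only self-reports. Participants are nowhere said to be masked, so self-report raises a separate question.

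It is also fair that a clinician must know the design, including that quasi-random assignment has ended, to infer the algorithm. The article does not say that they know. But it describes no step that would keep it from them, and the design is public.

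**Conclusion.** The concern holds as a wrong statement about the design. Masking of clinicians and peer coaches to the algorithm can hold for algorithm 1 versus quasi-random assignment in waves 1 and 2. It cannot be relied on for algorithms 2 and 3: two of four categories, and 50% of participants by the article's own shares (40% to 60% under the assumed range of wave sizes), with fewer actually having a clinician or coach rating.

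This rests on two premises: that clinicians and coaches know which wave they are working in, and that they know or can learn the published design. It does not rest on who attends the think tank.

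The consequence is limited to the CGI and fit ratings in comparisons that involve algorithm 2 or 3. The amount and direction of any bias there are unknown.

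**What to change.** - In Routing Procedures, limit the statement on masking to the algorithm, for care providers and peer coaches alike, to waves 1 and 2. Keep the statement on masking care providers to coaching for all waves.
- State that CGI and fit ratings count as masked evidence only for algorithm 1 versus quasi-random assignment.
- In any comparison involving algorithm 2 or 3, report these ratings as unmasked, non-concurrent and supportive.
- Say there too that self-report is not stated to be masked, so that moving the weight to self-report is not presented as a full remedy. Attendance is no clean substitute either, since clinicians and coaches record it.
- Add one sentence on whether treating clinicians and coaches take part in the think tank.

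The cost is wording only: no change to allocation, sample size or data collection. The price is that informant ratings carry less weight in cross-wave comparisons of algorithms.
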